### Participants

Participants will include 250 adults aged 50 years and older who have been registered with the state of Florida for at least 12 months to obtain medical marijuana and report use daily or most days of the week (n=125), as well as race-sex–matched participants with no marijuana use in the past 10 years and no history of daily use (n=125). Textbox 1 provides the inclusion and exclusion criteria. To examine age as an independent factor, we will ensure that age variability is balanced between the two groups. We selected a 10-year no marijuana exposure window to ensure that recreational use does not confound our findings. We chose to match participants by sex to ensure that sex differences do not account for driving performance outcomes. We also chose to match participants by race to ensure that differences in psychomotor functioning by race among older adults do not account for the findings. Groups will be balanced by age (±1 year) to allow for observation of group differences by age.

Inclusion and exclusion criteria.
**Inclusion criteria**
Aged 50 years and older who endorse chronic or severe nonmalignant painResident of Florida with an active and valid Florida driver’s licenseActive medical marijuana card for >12 months issued by the state of FloridaCan communicate in EnglishWilling and able to complete study proceduresRace-sex match who has not used marijuana in the past 10 years with no history of daily use
**Exclusion criteria**
Active psychosisLost or revoked driving privilegesScore below 24 (out of 30) on the Montreal Cognitive Assessment (MoCA)Control participant who tests positive for marijuana use by urine test or reports any marijuana use in the past 10 years

### Study Procedures

#### Screening

Participants referred to the study by MMTC, community-dwelling adults who self-nominate for participation, or those identified by our recruitment specialist will undergo preliminary screening for eligibility, including questions related to chronic or severe pain, frequency of medical marijuana use, date of last marijuana use, Florida medical marijuana card status, and Florida driver’s license status, as well as basic sociodemographic information. Once eligibility has been verified, participants will be scheduled for their first assessment session. They will be instructed to bring a valid Florida driver’s license, a valid Florida medical marijuana card (MMG only), and a list of all current prescription medications, over-the-counter medications, vitamins, and supplements with the names, doses, and frequency of administration for each. Screening IDs will be separate from participant IDs, which will be assigned after study enrollment and informed consent. Screening data will be used for the Consolidated Standards of Reporting Trials (CONSORT). Figure 1 provides the study flow.

#### Assessment Session 1 (Onboarding, Informed Consent, and Questionnaires)

At the AS1 study appointment, participants will be greeted by a study research assistant who will introduce the study and provide informed consent. Following informed consent, participants will be screened for cognitive fitness to proceed using the Mini-Mental State Examination–Second Edition Brief Version (MMSE-2:BV), a 16-item screener used to efficiently assess cognitive function [37], to ensure that participants are eligible for the study. If a participant scores fewer than 14 points on the MMSE-2:BV, the study team will administer the Montreal Cognitive Assessment (MoCA), a 30-item screener emphasizing attention and executive function that is used to detect cognitive impairment [38]. Participants must score at least 24 points on the MoCA to proceed. Participants will then complete an assessment battery that includes sociodemographic data and psychosocial measures, including detailed assessments of medical marijuana and other substance use, pain levels, and overall current health status. We will obtain the past 3-year driving record from the Division of Motor Vehicles using the current ROAD ACE protocol. Participants will be compensated US $50 for this assessment.

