Findings regarding the effects of long-term marijuana use are mixed. Some evidence indicates that long-term, heavy cannabis use (ie, daily or almost daily use) may cause impairment in cognitive and motor functions [24]. Long-term heavy use is associated with decreased motor control, decreased attentional control in both sustained and divided attention, greater cognitive impairment, and greater short-term memory deficits [24,25]. Current heavy use is also associated with decreased vehicle control [1]. However, some studies suggest that impairment due to long-term heavy use does not persist after extended abstinence periods and that mild to moderate use is not associated with impairment [26].

For mid- to late-life adults, participation in driving activities allows them to meet their social roles and stay independent [14,27,28]. Factors such as age-related functional impairments due to chronic pain and side effects of medications such as medical marijuana and prescription opioids can compromise participation in driving and lead to heightened crash risk [28-30]. In the United States in 2015, more than 85% of adults aged 65 to 84 years and nearly 70% of adults aged 85 years and older were licensed to drive [31]. By 2030, the number of older adults is projected to account for 21% of the US population, and most older adults will retain their driver’s licenses [32,33].

To date, no studies have systematically assessed driving performance in a rigorous and ecologically valid manner accounting for long-term medical marijuana use and the combined effect of prescription opioid use in adults aged 50 years and older, who endorse chronic or severe nonmalignant pain. Further, studies examining how older adults self-regulate prescription medication use and driving behavior are limited, with none rigorously examining medical marijuana.

Thus, the overall objective of this study is to address the research questions: Does daily long-term medical marijuana use affect performance on an open-road driving task in adults aged 50 years and older who endorse chronic or severe nonmalignant pain, and what is the combined effect of long-term medical marijuana and prescription opioid use on driving performance outcomes in this population?

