### Study Design

We are using a two-group observational study design with a group with medical marijuana use for more than 12 months daily or most days of the week (medical marijuana group [MMG]) versus a race-sex–matched group with no marijuana exposure in the past 10 years and no history of daily use (no marijuana group [NMG]). We chose 10 years as the no–marijuana-exposure window to ensure that recreational use was not a confounder. We will test the difference between long-term medical marijuana exposure and no marijuana exposure on driving performance outcomes in adults aged 50 years and older who endorse chronic or severe nonmalignant pain through an open-road driving assessment. There will be up to 3 in-person assessment sessions over approximately 10 days. Assessment session 1 (AS1; the first assessment session) is the onboarding session, which will include informed consent, sociodemographics, a battery of psychosocial measures, and urinalysis to test for the presence of marijuana, opioids, and other commonly misused substances. After AS1, we will use ecological momentary assessment to capture medical marijuana use (MMG) or mood and medication use (NMG). MMG participants will complete twice-daily assessments of medical marijuana use for 7 days. To attention match, the NMG will complete twice-daily assessments of mood and any medication use daily for 7 days. Assessment session 2 (AS2; the second assessment session), the open-road driving performance task, will occur approximately 8 days after AS1 and, for MMG participants, 8-12 hours after the last medical marijuana use. At AS2, vision screening to ensure appropriate visual acuity and urinalysis will be completed before the drive. Additionally, we will request permission from MMG participants only to extract Office of Medical Marijuana Use (OMMU) purchase history data, which include the dispensary name, date of purchase, quantity of medical marijuana purchased, and route of administration. Assessment session 3 (AS3; the third and final assessment session) will be a qualitative interview with a subset of participants (n=60) regarding self-regulation of medical marijuana and prescription medication use, to be completed no later than 3 days after the drive (Figure 1).

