#### Assessment Session 2 (Driving Performance Task)

Participants will arrive at the UF Smart House either by Uber or by a driver of their choice. For MMG participants only, AS2 will take place 8-12 hours after the last medical marijuana use. Upon arrival at the Smart House, a study team member will complete vision screening with the UFOV (Posit Science) and Optec 5000 (Stereo Optical) visual analyzer machine and collect a urine sample for urinalysis. A portion of the urine provided by MMG participants will be reserved for analysis using liquid chromatography–tandem mass spectrometry, which provides a more precise measurement of the level of THC-COOH, a metabolite of THC, present in urine. We will request permission from MMG participants only to extract OMMU purchase history data, which includes the dispensary name, date of purchase, quantity of medical marijuana purchased, and route of administration.

The CDRS or DRT will begin the open-road driving performance task evaluation, which begins with a standardized field sobriety test to detect the presence or absence of horizontal gaze nystagmus, the involuntary jerking or sudden eye movement that naturally occurs when the eyes gaze to the side [39]. The evaluator will instruct participants to focus on and follow the trajectory of a slow-moving horizontal object, typically a pen, presented directly in front of their face. The evaluator will observe both the right and left eye for 3 distinct signs: lack of smooth pursuit, distinct nystagmus at the maximum eye deviation (N_max_), and onset of nystagmus prior 45° deviation (N45) [40]. These signs will be recorded as “present” or “absent,” and participants will be classified as “failed” if all factors are noted as “present.” Participants who fail the sobriety test will be informed that they cannot complete the drive and will be compensated US $20 for a partial AS2 visit.

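### The cognitive screen sets eligibility at a visit with no stated since-last-use interval, so marijuana-related failures, possible only in the exposed group, can bias the comparison toward no effect

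*Protocol article*

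**What the plan says.** Under Assessment Session 1, cognition is screened after consent in two stages. The first is the MMSE-2:BV: "If a participant scores fewer than 14 points on the MMSE-2:BV, the study team will administer the Montreal Cognitive Assessment (MoCA"). The second is decisive: "Participants must score at least 24 points on the MoCA to proceed". Textbox 1 lists a MoCA score below 24 as an exclusion and does not restrict it to either group.

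The interval since last use is attached to the drive: "For MMG participants only, AS2 will take place 8-12 hours after the last medical marijuana use". Study Design says the same, and places the drive later: "the open-road driving performance task, will occur approximately 8 days after AS1". Screening asks for the "date of last marijuana use" but ties no limit to the answer and does not carry it forward to AS1.

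The exposed group is defined by "medical marijuana use for more than 12 months daily or most days of the week". The estimand text that follows Figure 1 says that the design should reflect long-term adaptation and real-world use, as opposed to acute intoxication. It also describes driving as one task that draws on cognition, memory and executive function. The Introduction links long-term heavy use to "decreased attentional control in both sustained and divided attention, greater cognitive impairment", within a paragraph that calls the evidence mixed.

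**The concern.** An eligibility test is being applied to a variable that the exposure may lower and that bears on the outcome. There are two routes. In the acute route, someone who uses on most days may come to AS1 soon after use, score lower for that reason, and be excluded in a state that the study does not set out to measure. In the long-term route, the exposure itself lowers cognition, and the screen then removes people who carry part of the effect under study.

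A member of the no-marijuana group (NMG) can fail for many reasons, but not for either of these. If marijuana does lower the screen score, the MMG loses more people at the low end, and the MMG members who reach the drive are better drivers on average than the group they stand for. The t test and the ANCOVA on the sum of maneuvers score (SMS) use only those who drove, so adjustment cannot undo this. An understated deficit is the costly error here, because the results are meant to feed risk screening.

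**Working it through.** **Text check.** Setting the AS1, AS2, Study Design and Screening sections side by side, the interval appears twice, both times for AS2. No section states one for AS1.

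**Size.** The article gives no screen failure rate, no correlation between cognition and SMS, and no effect of marijuana on the screen. There is therefore no plan figure to reproduce, and every input below is an assumption:

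- true MMG deficit in SMS: 0.40 SD on average;
- correlation ρ between cognition C and SMS: 0.3 or 0.5;
- average lowering s of the screen score in the MMG: 0.3 or 0.5 SD;
- each stage is cut at the NMG 5th percentile (z = -1.645), with test reliability 0.7.

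Model: stage score T = √0.7·C + √0.3·e - s·G, with s = 0 in the NMG. A person is excluded only if both stages fall below -1.645. SMS = ρC + √(1-ρ²)·e, minus 0.40·H in the MMG. G and H are individual sensitivities with mean 1: one shared exponential variable, two independent exponentials, or a constant 1 (uniform effect). There were 2,000,000 simulated people per group, and 2.0% of the NMG were excluded.

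| Sensitivity | s | MMG excluded | Retained difference, ρ = 0.3 / 0.5 |
|---|---|---|---|
| Shared | 0.3 | 5% | 0.37 / 0.36 |
| Shared | 0.5 | 9% | 0.325 / 0.31 |
| Independent | 0.3 | 5% | 0.39 / 0.38 |
| Independent | 0.5 | 9% | 0.38 / 0.36 |
| Uniform | 0.3 | 4% | 0.39 / 0.38 |
| Uniform | 0.5 | 6% | 0.38 / 0.36 |

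The range is 0.31-0.39 SD. With s = 0 the difference stays at 0.40.

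**Comparison with one cut.** If a single error-free cut replaced the two stages, with shared sensitivity, the MMG exclusion would be 9.9% (s = 0.3) or 15.0% (s = 0.5). The retained difference would be 0.33-0.35 or 0.27-0.30 SD.

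**Hand check of the mechanism** (single cut, uniform effect, s = 0.5). The mean of C above a cut k is φ(k)/(1-Φ(k)).

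- NMG, k = -1.645: 0.1031/0.95 = 0.109.
- MMG, k = -1.645 + 0.5 = -1.145: 0.2071/0.8739 = 0.237.
- Gap: 0.237 - 0.109 = 0.128. Retained difference: 0.40 - 0.3 × 0.128 = 0.36, or 0.40 - 0.5 × 0.128 = 0.34. The simulation gives 0.36 and 0.33.

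**Consequence for power** (normal approximation, assumed two-sided 5% level, 125 drivers per group). Power = Φ(d·√(125/2) - 1.96).

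- d = 0.40: Φ(3.16 - 1.96) = 0.89.
- d = 0.39: Φ(3.08 - 1.96) = 0.87.
- d = 0.31: Φ(2.45 - 1.96) = 0.69.

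**The case against.** **The article is a condensed text.** A fuller protocol may hold an instruction about use before AS1. That is fair, and it means silence cannot be read as permission. But the article does state the interval, twice, and ties it to AS2 each time. The long-term route would also remain under any AS1 interval.

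**The evidence is mixed.** The Introduction also reports studies in which impairment does not last after extended abstinence and mild to moderate use shows none. This stands: the bias is possible, not established.

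**The screen is lenient.** A person must fail both stages to be excluded, which keeps exclusions few. This also stands, and it is why the two-stage range is the one to quote.

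Four stronger readings are tempting, and the documents do not support them:

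- *The screen removes people from one group only.* It does not; the criterion covers both groups. Only failures caused by marijuana are one-sided.
- *The effect shrinks to below 0.30 SD.* Among the scenarios with a 0.40 SD deficit, that needs a single cut, the larger screen shift, and the assumption that those whose score drops at AS1 are the same people who drive worse 8-12 hours after use. No section supports that last link. Concentrating the whole effect in 20% of users gives still larger losses, but this too is pure assumption.
- *Participants consent or answer questionnaires while intoxicated.* Nothing in the article says so.
- *The mismatch over who takes the MoCA adds to the bias.* It does not; admitting people without a MoCA reduces exclusions.

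**Conclusion.** The concern holds as a design weakness of unknown size. Eligibility is decided at a visit for which the article sets no since-last-use interval, in a study that says it is not about acute intoxication. Exclusions caused by marijuana can arise in the MMG only, and in every scenario with a link between cognition and driving they move the SMS difference toward no effect. With the two-stage screen and the inputs listed above, 0.40 SD becomes about 0.31-0.39 SD, a loss of 0.01-0.09 SD. The figures are illustrations, not estimates and not bounds. If marijuana does not lower the screen score, there is no bias.

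A separate inconsistency stands on its own. Textbox 1 excludes on a MoCA score below 24, whereas the AS1 procedure gives the MoCA only to those below 14 on the MMSE-2:BV. Someone at 14 or more is never measured against the listed criterion.

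**What to change.** 1. Schedule AS1 visits for the MMG under the since-last-use condition that the protocol already sets for AS2, and record time of last use at AS1. The cost is less flexible booking for that group and one added question. This removes only the acute route.
2. If a repeat screen is allowed at all, allow it on the same terms in both groups. A second attempt for MMG failures alone would add a new asymmetry.
3. For the long-term route, report cognitive exclusions by group in the CONSORT flow that the Screening section already plans, and limit the conclusion to people who pass the screen. This costs a line in the flow diagram and a sentence in the report.
4. Reconcile Textbox 1 with the AS1 procedure so that one cognitive rule is stated. Which rule that should be is for the investigators to decide.

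As of November 2025, 30 of the planned 250 participants were enrolled, so a change now would cover about 250 - 30 = 220. Time of last use at AS1 may be hard to recover for those already seen.

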#### Assessment of Daily Use

After the AS1 study visit, participants will be instructed to track their medical marijuana or mood and medication use for 7 days at home. Participants will be prompted by Mosio, a HIPAA-compliant text messaging service supported by REDCap, to respond to use surveys twice per day by entering all medical marijuana use (MMG) and mood and medication use (NMG) for 7 days. The surveys will begin 7 days before AS2, with the final survey administered the evening before AS2. All data gathered by the Mosio platform (protected health information or non-protected health information) will be subject to the same security, privacy, and breach notification measures that apply to all entities subject to HIPAA standards, and the Mosio platform is bound by the business agreement established with Florida State University. Mosio may also be used to communicate other study-related messages to participants and within the research team. NMG participants will be compensated in the same manner as MMG participants for completing daily assessments of their mood and medication. Participants will be compensated US $10 per day, with a US $5 bonus for providing data for all 7 days.

#### Assessment Session 2 (Driving Performance Task)

Participants will arrive at the UF Smart House either by Uber or by a driver of their choice. For MMG participants only, AS2 will take place 8-12 hours after the last medical marijuana use. Upon arrival at the Smart House, a study team member will complete vision screening with the UFOV (Posit Science) and Optec 5000 (Stereo Optical) visual analyzer machine and collect a urine sample for urinalysis. A portion of the urine provided by MMG participants will be reserved for analysis using liquid chromatography–tandem mass spectrometry, which provides a more precise measurement of the level of THC-COOH, a metabolite of THC, present in urine. We will request permission from MMG participants only to extract OMMU purchase history data, which includes the dispensary name, date of purchase, quantity of medical marijuana purchased, and route of administration.

The CDRS or DRT will begin the open-road driving performance task evaluation, which begins with a standardized field sobriety test to detect the presence or absence of horizontal gaze nystagmus, the involuntary jerking or sudden eye movement that naturally occurs when the eyes gaze to the side [39]. The evaluator will instruct participants to focus on and follow the trajectory of a slow-moving horizontal object, typically a pen, presented directly in front of their face. The evaluator will observe both the right and left eye for 3 distinct signs: lack of smooth pursuit, distinct nystagmus at the maximum eye deviation (N_max_), and onset of nystagmus prior 45° deviation (N45) [40]. These signs will be recorded as “present” or “absent,” and participants will be classified as “failed” if all factors are noted as “present.” Participants who fail the sobriety test will be informed that they cannot complete the drive and will be compensated US $20 for a partial AS2 visit.

After sobriety is ascertained, the task continues with a “warm-up” period using a dual-brake program vehicle (a 2019 Toyota Camry or 2020 Toyota Corolla) in a parking lot. The evaluator will review the general controls for mirrors, seats, and automatic transmission shift. Drivers will perform simple maneuvers and practice perpendicular or angled parking for approximately 3 minutes. The course is designed to progress from simple to moderate and then high-complexity environments. The parking lot or “off-road” area transitions directly into a residential or simple driving environment. To ensure adequate exposure within each level of difficulty, the course is designed to include at least 3 examples of each type of maneuver within each level of difficulty. Multimedia Appendix 1 contains road course documentation and scoring details. The assessments will take place during daylight hours from mid-morning through late afternoon—approximately 9 AM to 4 PM. Assessments will be cancelled if the clinical evaluator deems the conditions unsafe due to inclement weather or unsafe road conditions. The complete course consists of 49 maneuvers through Gainesville, Florida. The driving performance form is designed so a single evaluator can document observed driving errors adequately and remain attentive to the driver and surrounding conditions. The fixed route ensures all participants are given the same maneuvers. The evaluator will check observed errors from a list of behaviors under each maneuver. The SMS is the total number of points accumulated over the set number of maneuvers divided by the total possible number of points (49 maneuvers × 3 = 147 possible points, indicating perfect driving). Participants will be compensated US $50 for this assessment and an additional US $20 as a transportation supplement for expenses such as gas or rideshare fees spent traveling to the Smart House.

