### Sample Size and Power

Power estimates for this study are based on the number needed for the subanalysis to ensure we have sufficient power to answer aim 2. Using G*Power for the *F* test, we calculated the sample size for a small effect size (*f*=0.20) based on the expectation of a smaller effect size for subgroup analyses than for the main analyses [36]. Therefore, with an α of 0.5 and power set at 80%, a total sample size of 198 is needed to detect a small effect between subgroups of medical marijuana only, medical marijuana and prescription opioids, prescription opioids only, and no use at all. However, to ensure we have the full sample needed, we are planning for a potential early termination rate (eg, drive not completed due to intoxication or other reasons) of 5%, which indicates we need a sample size of 250—as 198 + 10 (5%) = 250 (125 per group). We anticipate a medium effect size for aim 1 based on the first ROAD ACE (Reactions of Older Adults Driving After Cannabis Exposure) project (1R21DA048067) that examined driving errors and medical marijuana 7-day pattern of use in a driving simulator. We found a Pearson *r*=0.459, which is equal to a medium effect size (see preliminary data above). Therefore, we will have sufficient power to test the effects in aims 1 and 2.

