### Safety Monitoring

#### Primary Outcome

The safety of all participants will be ensured through: (1) sobriety testing, (2) vision screening, (3) no drives conducted in rainy conditions, (4) all drives completed during daylight hours during and periods of lower traffic congestion, and (5) use of a dual-brake controlled vehicle equipped with an eye check mirror for the CDRS or DRT. In addition, a closed-road driving observation period will be conducted by the CDRS or DRT, during which any safety concerns will result in termination before entering the open road. The CDRS or DRT will provide verbal cues as needed and take over steering if necessary to prevent harm, as trained and in accordance with best practices.

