### Alternative Design Plan

Limitations may be related to the distribution of the dependent variable, as ANCOVA has strict assumptions. An alternative plan would be to use generalized linear mixed models, which can handle non-Gaussian data, correlated data, unbalanced data, and address missing data while still maintaining power. Possible mitigation approaches include creating a dichotomous variable of high versus low for outcomes and using logistic generalized linear mixed model regression or other functional form as dictated by the distribution of the dependent and independent variables.

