### Missing Data

Regarding missing data, we will also perform sensitivity analyses to assess the impact of missing data. Further, we will perform appropriate secondary analyses to adjust for variables that may be related to systematic missingness.

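### Participants stopped before the scored course have no SMS and are handled as a 5% attrition allowance, although closed-road safety stops depend on driving itself; non-completion should be reported by reason and group, with a pre-specified worst-rank sensitivity analysis

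*Protocol article*

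**What the plan says.** Two rules end a participant's session before the scored course:

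- Assessment Session 2 (Driving Performance Task): "Participants who fail the sobriety test will be informed that they cannot complete the drive". Failure means that all the eye-movement signs are present.
- Safety Monitoring, on the closed-road observation: "any safety concerns will result in termination before entering the open road".

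Under Scoring Criteria, the SMS (0 to 147) is totalled over 49 maneuvers when the course ends. A maneuver that needs verbal cues scores 1, and one that needs physical intervention scores 0.

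Sample Size and Power treats these stops as early termination, giving as its example "drive not completed due to intoxication or other reasons". It allows 5% overall and does not divide this between the groups. Data Analysis Plan and Hypothesis 1a and 1b then compare SMS between the MMG and the no marijuana group (NMG) by t test and ANCOVA.

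Missing Data promises sensitivity analyses in general terms, and secondary analyses to "adjust for variables that may be related to systematic missingness". Alternative Design Plan adds that mixed models can "address missing data while still maintaining power". No section says what value or rank a stopped participant receives.

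**The concern.** A closed-road stop is the evaluator's judgment that the person is not driving safely, which is close to what the SMS measures. A driver who needs intervention on the course keeps a low score, while a driver judged too unsafe to start has none. Enlarging the sample replaces the lost numbers but does not undo the selection.

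The two remedies named in the plan fall short for different reasons. Covariate adjustment corrects only for what measured variables explain, not for loss driven by the unobserved score. A mixed model recovers information from a participant's other outcome measurements, and here each participant has one SMS, so a person without it contributes nothing.

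If use worsens driving, more MMG participants would be expected to meet a safety stop, and a completer comparison would then be pulled toward no difference. In a study meant to inform risk screening, a null result could not be separated from this selection.

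**Working it through.** **The plan's own figure.** Sample Size and Power states: "with an α of 0.5 and power set at 80%, a total sample size of 198 is needed", for f = 0.20. With two equal groups, d = 2f = 0.40. Taking α as 0.05, n per group = 2(1.960 + 0.842)²/0.40² = 98.1, so 99 per group and 198 in total (noncentral F gives 199). With the printed α of 0.5 the same test would need 54. The base of 198 therefore reproduces only at α = 0.05 and one degree of freedom.

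The allowance is printed as "we need a sample size of 250—as 198 + 10 (5%) = 250 (125 per group"). But 198 × 1.05 = 207.9 and 198/0.95 = 208.4, so 5% leads to 208 or 209. A total of 250 implies a loss of 1 − 198/250 = 20.8%. These are separate errors. What matters here is the stated 5%: 0.05 × 250 = 12.5, or about 12 to 13 people.

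**Which events lose the score**

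| Event | Before scored course? | Depends on driving? | SMS available? |
|---|---|---|---|
| Failed sobriety test | yes | no, eye-movement signs | no |
| Closed-road safety concern | yes | yes | no |
| Cue or intervention on the course | no | yes | yes (1 or 0 for that maneuver) |
| Drive ended part-way | no | may be | not described |

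**Size.** The article gives no SD of SMS, no stop rates by group and no link between stopping and SMS, so all three are assumed. Let SMS have SD 1, with the MMG worse by 0.40. In each group the fraction q lowest on a stopping tendency is stopped, and that tendency has correlation ρ with SMS. The completers' mean then rises by ρ·s(q), where s(q) = φ(z_q)/(1 − q), and

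observed difference = 0.40 − ρ[s(q_MMG) − s(q_NMG)].

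- s(0.025) = 0.0584/0.975 = 0.060
- s(0.075) = 0.1416/0.925 = 0.153
- s(0.10) = 0.1755/0.90 = 0.195
- s(0) = 0

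Change in the difference, with 5% stopped overall and 125 per group:

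| Stopped, MMG / NMG | ρ = 0 | ρ = 0.3 | ρ = 0.6 | ρ = 1 |
|---|---|---|---|---|
| 5% / 5% | 0 | 0 | 0 | 0 |
| 7.5% / 2.5% | 0 | −7% | −14% | −23% |
| 10% / 0% | 0 | −15% | −29% | −49% |

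For example, 10%/0% at ρ = 0.6 gives 0.40 − 0.6 × 0.195 = 0.283, which is −29%. Simulation of the bottom right cell gave −48%.

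Power with everyone scored is about 0.88. It falls to about 0.82, 0.79 and 0.74 in the second row (ρ = 0.3, 0.6, 1), and to about 0.75, 0.61 and 0.40 in the third.

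**Would loss be unequal?** Apply one threshold c to both groups, with 5% stopped overall: [Φ(c) + Φ(c + 0.40)]/2 = 0.05 gives c = −1.877. This stops 3.0% of the NMG and 7.0% of the MMG. Here s = 0.071 and 0.144, a gap of 0.073, so the attenuation is about 6%, 11% and 18% at ρ = 0.3, 0.6 and 1. Under this model, a real effect of use on driving is enough to make the loss unequal.

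**The case against.** **Group split.** A reader might infer that the stops fall mostly in the MMG and that the result is therefore biased toward no effect. The article does not support this as a statement of fact. The 5% is not split, neither stop rule is limited to one group, and opioid-positive participants in either group may drive. With equal or unrelated loss the bias is near zero. This objection stands, and the point is worded conditionally.

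**Size.** A reader might quote the extreme in which the MMG loses exactly its worst 5% and the NMG loses nobody: a shift of 0.109 SD, with power falling from 0.80 to about 0.51 for a true difference of 0.36 SD. That is one corner of the range. The article also expects a medium effect for aim 1. At d = 0.50, the 7.5%/2.5% split costs 6% to 19% and leaves power of at least 0.93.

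**Sobriety failures.** Study Design aims at long-term use rather than acute intoxication, so leaving these participants out of the primary analysis is defensible. This stands for sobriety failures but does not cover closed-road safety stops.

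**Exclusion is inferred.** The article never says that stopped participants are dropped. It promises sensitivity analyses, and an analysis plan or the scoring appendix, neither shown, may say more. That is fair. Even so, the article itself fixes the stop rules, the allowance, the primary tests and the remedies it names, and together these amount to a completer comparison.

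**Covariates help.** The visual tests, urinalysis, driving record and daily-use data are collected before the drive and could support weighting or imputation. They could remove part of the bias, but not the part that depends on the unseen score.

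**Conclusion.** The point holds in a limited form. Participants stopped before the scored course have no SMS, and the primary analyses as written can use only those who have one. For closed-road safety stops the loss is related to the outcome, and the named remedies cannot fully correct it. Bias toward no difference follows if stopping tracks poor driving and is more frequent in the MMG. The article establishes neither condition.

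At an assumed d of 0.40 with 5% stopped overall, attenuation is 0% with equal or unrelated loss, about 6% to 29% in intermediate cases, and 48% to 49% if all stops are exactly the worst MMG drivers. These figures rest on a normal model and assumed stop rates. The documents do not support reading this as a demonstrated bias, or as a reason to make a worst-rank analysis primary. It is a cheap improvement worth making while recruitment is still early (30 enrolled, completion expected by 2029).

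**What to change.** 1. Record each non-completed drive by reason: sobriety failure, closed-road or on-road safety stop, or weather, vehicle and other. Report the counts by group beside the primary result.
2. Pre-specify a rank-based sensitivity analysis, such as proportional-odds regression or rank ANCOVA with the primary covariates, that places safety-related stops at the worst rank.
3. Add a second version that also places sobriety failures at the worst rank. Keep it separate, because the estimand is set apart from acute intoxication.
4. Treat only stops unrelated to driving as ordinary missing data.

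Do not enter 0 for undriven maneuvers in the t test or ANCOVA. On the form, 0 records a physical intervention that in these cases never took place, and a few zeros would dominate the variance. As an illustration with an assumed mean of 130 and SD of 10, three zeros among 125 give a mean of 122 × 130/125 = 126.9 and an SD of √[(122 × (10² + 3.12²) + 3 × 126.88²)/124] ≈ 22.

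The cost is some analysis-plan wording, a reason code known at the visit and one extra analysis in two versions. The downside is a composite rank that is harder to interpret than a mean SMS difference. No stopping or safety rule needs to change.
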